#### Sample Size Calculations

A series of power analyses were performed to estimate the sample size required to detect a small interaction effect between time and type of intervention (the estimated effect size=−0.1) on student’s number of weekend drinks. The target was at least 80% power. Given that we are only interested in 2 estimated effects (ie, the main effect intervention and the interaction effect between time and intervention), a Bonferroni-adjusted family wise alpha of .025 was assumed for the power analysis [53]. All the analyses were conducted using R (R Foundation for Statistical Computing) and were based on a dataset obtained from a previous pilot experimental study [15].

Taking a conservative approach, we first estimated the sample size for a GEE with the main effects of time, type of intervention (ie, treatment), their interaction, and the main effects of gender and baseline alcohol consumption (ie, baseline). To this end, we used the GEE and long-power packages to estimate the minimum sample size required [54,55]. The results of analysis suggested a sample size of 527 to 553 students based on assuming an unstructured or an exchangeable correlation matrix.

Next, based on Monte Carlo simulations and using the estimated sample size required for the GEE analysis (ie, 553), we evaluated the power of performing GLM analysis. All the analyses were performed using the lme4 and simr packages in R [56,57]. First, we fitted a 2-level mixed effect model with the fixed effects of time, type of intervention (ie, treatment), their interaction, gender and baseline alcohol consumption (ie, baseline), and the random effect of student. The simulation results revealed a statistical power 97%, with 95% CI=91.48-99.38. Moreover, for a 3-level mixed effect model with the fixed effects of time, type of intervention (ie, treatment), their interaction, gender and baseline alcohol consumption (ie, baseline), and the random effects of student and college, the results of simulation showed a statistical power 98%, with 95% CI=92.66-99.76. Hence, our analysis suggested that a sample of 553 students would provide sufficient power for either 2- or 3-level mixed effect models.

Finally, considering an additional 25% dropout rate [15], we came up with a final target sample size of 692 students (the pilot dataset and the details of power analyses, eg, R codes, results, and power curve plots are available upon request from the first or last author).

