To date, 2 pilot studies provide some support for the efficacy of EMI messages during Orientation Week [15,38]. For example, in a pilot study, first-year students were randomized into an assessment-only condition or an EMI condition. Those in the assessment-only condition reported their drinking during Orientation Week and weekly during the academic year via ecological momentary assessments (EMAs), whereas those in the EMI condition reported their drinking and received daily EMI messages during Orientation Week. The EMI messages were sent at 7:30 PM (about the time students report drinking during Orientation Week), and the content of the messages alternated between the potential health-related and social consequences of alcohol use. The initial pilot found that women (but not men) in the EMI condition consumed significantly fewer drinks than women in the assessment-only condition during both Orientation Week (17 vs 26) and weekly during the academic year (5 vs 8) [38]. Following a series of focus groups with pilot study participants, the EMI was adapted so that messages were only sent on nights with large social events and 2 messages, rather than 1, were sent on these nights. When testing these changes in a second pilot-experimental study, students attending a relatively light drinking residential college consumed significantly fewer drinks relative to an assessment-only group during both Orientation Week (10 vs 16) and a typical academic year weekend (4 vs 7). The EMI, however, had no effect on students attending a residential college with a heavier preuniversity drinking pattern during either Orientation Week (38 vs 37) or the academic year (11 vs 9) [15]. Although these preliminary findings are promising, they have only been successful at reducing lighter drinkers’ alcohol use, suggesting that an EMI alone may not be not effective for all incoming students.

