## Methods

### Study Design

The study is a 3-arm RCT. Participants will be randomized into either a WBI+EMI condition, a WBI-only condition, or an assessment-only condition (Figure 1). The WBI will be administered before the start of Orientation Week, whereas the supplemental EMI will be delivered in 2 phases: 8 messages over 4 days during Orientation Week, and 6 messages during first semester. Participants will complete surveys at baseline (before Orientation Week) and after their first (~4 months) and second semester (~8 months).

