### Objectives and Hypotheses

The aim of the study was to test the effect of a WBI+EMI among incoming first-year students in New Zealand. The primary hypothesis was that participants in the WBI+EMI group will consume significantly fewer drinks during weekends in their first semester at university compared with those in WBI-only or assessment-only groups. Secondary hypotheses are that, when compared with those in the WBI-only and assessment-only groups, participants in the WBI+EMI group will report consuming fewer drinks during Orientation Week, and report experiencing fewer negative alcohol-related consequences, report lower Alcohol Use Disorder Identification Test-Consumption (AUDIT-C) scores, and less typical week alcohol use (at both 4 and 8 months follow ups). We also hypothesize that those in the WBI-only condition will consume significantly fewer drinks during weekends in their first semester at university, report consuming fewer drinks during Orientation Week, report experiencing fewer negative alcohol-related consequences, and report lower AUDIT-C scores compared with participants in the assessment-only group.

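### The sample size is built on one intervention effect, so the stated 80% power and alpha of .025 are not tied to the two comparisons that the three-arm primary hypothesis makes

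*Protocol article*

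**What the plan says.** Under Study Design, the protocol article states: "Participants will be randomized into either a WBI+EMI condition, a WBI-only condition, or an assessment-only condition". Under Objectives and Hypotheses, the primary hypothesis is that the WBI+EMI group will "consume significantly fewer drinks during weekends in their first semester at university compared with those in WBI-only or assessment-only groups". That names two pairwise comparisons.

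The Sample Size Calculations section works with one effect, a "small interaction effect between time and type of intervention (the estimated effect size=−0.1". It adds: "The target was at least 80% power". It justifies dividing alpha by two as follows: "Given that we are only interested in 2 estimated effects (ie, the main effect intervention and the interaction effect between time and intervention". The resulting alpha is .025.

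The power analyses "were based on a dataset obtained from a previous pilot experimental study [15". The Introduction reports that pilot as a comparison of EMI with assessment-only: "students attending a relatively light drinking residential college consumed significantly fewer drinks relative to an assessment-only group". It mentions no WBI arm.

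The GEE calculation gives 527 to 553 students, depending on the correlation structure. At 553, simulated mixed-model power is 97% (95% CI 91.48–99.38) with two levels and 98% (92.66–99.76) with three. An allowance for 25% dropout takes the target to 692. The section gives no per-arm number, pairwise contrast or three-group coding.

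**The concern.** With three groups, the intervention term needs two coefficients, and so does its interaction with time. The section counts one of each. Its Bonferroni division separates the main effect from the interaction and leaves nothing for the two comparators.

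This count, the single effect size and the two-group pilot all point to a two-group calculation whose total was carried over to a three-arm trial. In that case each comparison of WBI+EMI with one comparator draws on about two thirds of the students, not all of them.

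The comparison with WBI-only is the test of what the text messages add. A non-significant result there could be read as no benefit from a trial credited with at least 80% power, when power for that contrast may have been well below 80%.

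**Working it through.** **Inputs from the protocol article:** three arms; two primary contrasts; alpha .025; GEE total N₀ = 553 or 527 for 80% power; mixed-model power 97% and 98% at 553; target 692; dropout 25%.

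**Assumptions not in the article:** N₀ is a two-group 1:1 total with power of exactly 80%; the test is two-sided; the trial allocates 1:1:1; the true effect is the same for both contrasts.

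**Reproducing the plan's figures.** The 527–553 cannot be rebuilt, because the SD, the correlations and the scale of −0.1 are not given. Read as a standardized difference of 0.1, a plain two-group formula at 80% power and two-sided .025 needs 3804 students, so −0.1 is not on that scale. The check therefore starts from N₀ and rescales. The 692 reproduces as 553 × 1.25 = 691.25, rounded up. After 25% dropout, 692 × 0.75 = 519 remain, fewer than 553 (553/0.75 would be 738). That is a separate matter from the number of arms, so results for 553, 519 and 692 are kept apart.

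**Formula.** At N₀, the noncentrality is z(0.9875) + z(0.80) = 2.241 + 0.842 = 3.083. With N analysed in three equal arms, a pairwise contrast uses 2N/3 students:

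noncentrality = 3.083 × √((2N/3)/N₀); power = Φ(noncentrality − 2.241)

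**GEE, power per contrast at two-sided .025**

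| N analysed | N₀ = 553 | N₀ = 527 |
|---|---|---|
| 553 | Φ(2.517 − 2.241) = 60.9% | Φ(2.579 − 2.241) = 63.2% |
| 519 | Φ(2.439 − 2.241) = 57.8% | Φ(2.498 − 2.241) = 60.1% |
| 692 | Φ(2.816 − 2.241) = 71.7% | Φ(2.885 − 2.241) = 74.0% |

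**Mixed model, same scaling from N₀ = 553.** The starting noncentrality is 2.241 + z(reported power).

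| Reported power at 553 | Starting noncentrality | 553 analysed | 519 analysed |
|---|---|---|---|
| 97% | 4.122 | 87.0% | 84.6% |
| 98% | 4.295 | 89.7% | 87.6% |
| 91.48% (lower limit of the 97% figure) | 3.612 | 76.1% | 73.1% |

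**Alpha.** Two contrasts on each of two effects make four coefficients, and .05/4 = .0125. At .0125, GEE power (N₀ = 553) is 50.8% with 553 analysed and 47.6% with 519. At an unadjusted .05 it is 71.1% and 68.4%, and it reaches 80.4% only with all 692 analysed.

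**Smallest effect with 80% GEE power at .025.** The effect scales as √(N₀/(2N/3)). With N₀ = 553 it is 0.1 × √(553/368.7) = 0.122 for 553 analysed and 0.1 × √(553/346) = 0.126 for 519, on the plan's own scale.

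**The case against.** The strongest reply is that two-group coding is nowhere stated. The power model uses the same term, type of intervention, as the three-arm analysis model; the R code is offered on request and is not shown; and the pilot is only summarised. This stands: two-group coding is an inference, and the GEE percentages depend on it. It does not rescue the count of two effects, which does not fit a three-level factor whatever the code did.

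A reader might infer that every primary comparison has only 58–60% power. The documents do not support that, for three reasons:

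- The figure applies to the GEE alone. The Statistical Analysis section plans both GEE and the mixed model, and the mixed-model point estimates stay above 80% after the same scaling. They are not decisive either: they appear to rest on the same single treatment term and the same pilot, and the lower limit of the 97% figure scales to below 80%.
- It combines the three-arm split with the dropout allowance. The split alone gives 61–63%.
- The 519 treats every dropout as contributing nothing. Partial responders in a repeated-measures model do contribute, so 519 is a lower bound under the stated dropout.

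A reader might also infer that the trial must win on both contrasts. The Abstract and Data Treatment join the comparators with 'and', while Objectives and Hypotheses uses 'or'. No decision rule requires both, so a joint power figure would rest on a rule that the article does not set.

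**Conclusion.** The point holds in limited form. As written, the sample size justification does not match the design: it counts one main effect and one interaction where three arms give two of each, and neither its power nor its alpha refers to the two primary contrasts.

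The size of the shortfall is conditional. On the GEE calculation that set N, under the assumptions listed above, power per contrast is about 61–63% with 553 analysed, within a range of 58% (519) to 74% (692). For the mixed model, a shortfall below 80% is possible but not shown. If the calculation already used three arms, no power is lost and only the description needs correcting. The article alone cannot settle which case applies.

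**What to change.** Re-run the existing GEE and mixed-model power code with three arms and the two contrasts of WBI+EMI against each comparator, with alpha allocated to those contrasts, at 692 randomized and 25% dropout. In the text:

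- state the group coding, the allocation ratio and the expected number per arm;
- correct the count of effects;
- replace the single 80% claim with power per contrast for each planned model;
- give the smallest effect detectable with 80% power at the expected per-arm number;
- give joint power only if success is defined as winning on both contrasts.

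The article says that the pilot dataset and R code exist, so the cost is a re-run and a revised paragraph. No added enrolment is asked for. The only downside is that the stated power may look less favourable.

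### The 692 target multiplies 553 by 1.25 instead of dividing by 0.75, so 25% dropout leaves 519 students, fewer than either end of the stated GEE requirement (527 to 553)

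*Protocol article*

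**What the plan says.** All of the sample size figures are in the protocol article, Sample Size Calculations.

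- Power and alpha: "The target was at least 80% power", and "a Bonferroni-adjusted family wise alpha of .025 was assumed for the power analysis". The effect is a time-by-intervention interaction on weekend drinks ("the estimated effect size=−0.1").
- GEE requirement: "The results of analysis suggested a sample size of 527 to 553 students based on assuming an unstructured or an exchangeable correlation matrix".
- The upper figure goes into the mixed-model simulations ("using the estimated sample size required for the GEE analysis (ie, 553"). These gave 97% power for the 2-level model (95% CI 91.48 to 99.38) and 98% for the 3-level model (95% CI 92.66 to 99.76). The section concludes that "our analysis suggested that a sample of 553 students would provide sufficient power for either 2- or 3-level mixed effect models".
- Dropout comes last: "considering an additional 25% dropout rate [15], we came up with a final target sample size of 692 students".

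The formula for the last step is not written out. Nothing in the article says that dropout was already built into 527 to 553.

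The Data Treatment section adds that the intention-to-treat analysis covers everyone assigned, with multiple imputation, and that a complete-case analysis will also be shown.

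**The concern.** A dropout rate applies to the number enrolled. If a fraction d is lost, enrolling N leaves N(1 − d), so the enrolment that leaves n is n / (1 − d). Multiplying n by (1 + d) always gives too few, and at d = 0.25 the gap is noticeable. The final target looks like the product of that shortcut.

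At stake is whether the enrolment figure does what the section uses it for, which is to protect the required sample against the stated dropout. If it does not, readers will credit the trial with more tolerance of dropout than it has, and the GEE power after dropout would sit somewhat under the 80% aim.

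**Working it through.** **Inputs, all from Sample Size Calculations.** GEE requirement 527 to 553; base carried forward 553; dropout 25%; final target 692; power aim 80%; alpha .025 (sidedness not stated).

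**1. Reproduce the plan's figure.**
- n × (1 + d) = 553 × 1.25 = 691.25, rounded up to **692**: an exact match.
- 527 × 1.25 = 658.75, rounded up to 659: no match.

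**2. Apply the stated dropout to the stated target.**
- 692 × (1 − 0.25) = **519**.
- Against 553: 553 − 519 = 34 short.
- Against 527: 527 − 519 = 8 short.

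**3. Inflate correctly, n / (1 − d).**
- 553 / 0.75 = 737.3, so **738** (738 − 692 = 46 more).
- 527 / 0.75 = 702.7, so **703** (703 − 692 = 11 more).

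**4. Dropout that 692 can absorb, 1 − n / 692.**
- For 553: 1 − 553/692 = **20.1%**.
- For 527: 1 − 527/692 = **23.8%**.

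**5. GEE power at 519.** Assumptions: power is exactly 80% at the required size, the test is two-sided at .025, the normal approximation holds, and dropouts supply no outcome data. Then power = Φ[(z₁ + z₂)√(519/n) − z₁], with z₁ = 2.2414 and z₂ = 0.8416, so z₁ + z₂ = 3.0830.
- n = 553: 3.0830 × √(519/553) − 2.2414 = 0.745, giving **77.2%**.
- n = 527: 3.0830 × √(519/527) − 2.2414 = 0.818, giving **79.3%**.
- If .025 is one-sided, the results are 77.5% and 79.4%.

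**6. Mixed-model power at 519, same scaling.** This also assumes that the simulations used two-sided alpha .025.
- 97% at 553 becomes about 96%.
- The lower confidence limit for that model, 91.48%, becomes about 90%.

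**Not checked.** The 527 to 553 range itself cannot be rederived, because the pilot variances and correlations are not given. Steps 1 to 4 do not depend on them.

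**The case against.** The case on the other side concedes the arithmetic and disputes the consequence. Most of it stands.

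- **Dropouts are not necessarily lost to the analysis.** The primary outcome is built from up to six fortnightly reports in semester 1 (Table 1), and the intention-to-treat analysis includes everyone assigned. A student who stops halfway still contributes earlier reports. So 519 is the number retained, not necessarily the number analysed, and 77% to 79% is nearer a lower bound for that analysis than an estimate. Imputation does not replace outcomes from students who never report. For partial responders, though, the observed reports were never lost. The article does not use this to justify a smaller allowance, so it limits the consequence without removing the error.
- **Only the GEE calculation is affected in any way that matters.** The mixed models planned alongside it have ample reserve (step 6).
- **The choice of working correlation matters about as much.** It moves the requirement by 553 − 527 = 26 students, close to the 34-student shortfall.
- **The 80% aim is not expressly tied to the position after dropout.** The section states the aim and adds the dropout allowance later. Reading them together is reasonable, but it is an inference.

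One could also take the 25% as plain over-recruitment. That is weak, because the text calls it a dropout rate and cites the pilot study for it.

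A reader might infer that the trial as a whole is underpowered, or that every planned analysis misses 80%. The documents do not support that. The mixed-model results contradict it, and the GEE shortfall depends on dropouts' data being wholly lost.

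**Conclusion.** The final target is wrong as a 25% dropout allowance: 692 should be 738, or 703 if the lower GEE requirement is used. With 25% dropout, 692 retains 519 students, below both ends of the plan's own range. This part is arithmetic on printed figures and needs no outside assumption.

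The effect on power is small and conditional. GEE power falls by about 1 to 3 points below 80%, given exactly 80% at the required size, the normal approximation at .025, and no usable data from dropouts. Partial reports would shrink that loss. No analysis or error rate changes. The point is a minor correction of a stated figure, and it does not cast doubt on the trial's design.

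**What to change.** Amend the last paragraph of Sample Size Calculations in one of two ways.

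1. **Keep 692 and restate what it delivers.** It retains 519 students after 25% dropout and tolerates about 20% dropout against the requirement of 553 (about 24% against 527). It gives about 77% to 79% GEE power if dropouts' data are wholly lost. Limit the power statement to GEE and keep the condition in it. The cost is one sentence and no extra recruitment.
2. **Give the correctly inflated figure,** 553 / 0.75 = 738, as what the plan's own GEE criterion needs. If it also becomes the recruitment target, the cost is 46 more students. At the NZ $100 offered per participant, that is up to 46 × 100 = NZ $4,600 in remuneration.

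The article says that recruitment had begun but was not complete at submission, so both were open then. Given the size of the effect, the first is sufficient.

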## Discussion

### Summary

As noted above, the transition to university is associated with an increase in alcohol consumption [9]. One factor that contributes to this increase is Orientation Week [14-16]. Indeed, research on Orientation Week suggests that new students double their drinking relative to a typical week before university [14] and experience 5 times as many negative alcohol-related consequences [17]. With the aim of curbing these increases in consumption and harm, this protocol outlines a large-scale long-term RCT to test a WBI+EMI intervention.

### Limitations

This study is not without limitations. First, although the WBI provides individually tailored feedback, the content of the EMI messages is only tailored to the student’s gender. It is, however, important to remember that EMI messages were developed based on feedback from surveys [38], focus groups [15], and in-situ interviews with students outside Orientation Week events [18]. A second limitation is that there is a high degree of contact required for the assessment-only condition. It is possible that, due to regularly being asked to report how much alcohol they have consumed, participants in the assessment-only condition will reduce their levels of alcohol consumption and harm. Typically, participants in assessment-only control conditions are assessed at baseline and then at the end of the study. In this study, the assessment-condition consists of 2 assessment messages during Orientation Week and fortnightly assessment messages during the academic year (in addition to the baseline and follow-up assessments). The benefit of this approach is that we can compare the 3 arms of this RCT with a great deal of temporal precision. The limitation of this approach is that any effects observed will likely be smaller than those observed if we simply conducted a baseline assessment and long-term follow-up.

### Conclusions

This study adds to a growing body of work investigating the utility of WBIs and EMIs in curbing alcohol consumption. In addition, the study will help to inform policy approaches aimed at curbing alcohol consumption and alcohol-related harm in university students.

## Abbreviations

AUDIT-C: Alcohol Use Disorder Identification Test-Consumption
EMA: ecological momentary assessment
EMI: ecological momentary intervention
GEE: generalized estimating equations
GLM: generalized linear models
GMM: growth mixture modeling
OLS: online survey
PBS: protective behavioral strategy
SC: social consequence
WBI: Web-based intervention
